## Abstract

Research on support for relatives of patients with Parkinsonism has mainly focused on caregivers, while preventive offers for non-caregiving relatives are lacking. Thus, the aim of this multicenter pilot study is to develop and assess the feasibility of a preventive psychosocial support program for relatives of patients with Parkinsonism. It specifically focuses on family members of patients who are in an early phase of the disease, are not currently caregiving, and have not yet developed distress symptoms. It includes a telemedicine-based, 6-week preventive psychological short intervention (PPSI). The main objective of this feasibility mixed-methods study is to specify the demand for an early, low-threshold, and low-cost short intervention and to collect feedback based on qualitative and quantitative data of *N* = 20 relatives. Secondary objectives are an evaluation of the effects of the intervention and an analysis of the study design. Future directions are to further develop the PPSI using these data. This study can serve as a basis for future randomized controlled studies on this intervention, which might fill an important gap in clinical supply.

## 1. Introduction

Parkinson’s disease (PD) is the second most common neurodegenerative disease, and its prevalence is expected to increase substantially in the coming years [1]. PD is mostly characterized by the cardinal motor symptoms of bradykinesia, rigidity, postural instability, and tremor [2]. In addition, several other motor and non-motor symptoms affect patients’ and their relatives’ lives. The non-motor symptoms comprise constipation, orthostatic hypotension, bladder dysfunction, sexual dysfunction, depression, anxiety, or cognitive impairment, among many others. Age is currently considered the main risk factor [3]. Neuropathologically, the disease is based on the degeneration of dopaminergic neurons of the substantia nigra pars compacta [3]. As the disease progresses, the motor and non-motor symptoms can increasingly restrict patients’ daily lives and may require a substantial amount of care [4].

The diagnosis of PD, but especially the rampant restrictions in daily life while the disease progresses, may entail major psychological implications for the affected person and relatives.

In many cases, loss of patients’ autonomy and difficulties coping with daily life (clothing, personal hygiene, nutrition, mobility, taking medication, etc.) may inevitably cause an increased level of dependence on the relatives’ support. A growing body of literature indicates that the symptom burden of PD patients and stress experienced by family caregivers strongly correlate [5,6,7,8]. 

Research indicates that many families try to ensure care in the familiar home environment for as long as possible. Especially at early stages, care is usually provided exclusively by close family members such as spouses, children, siblings, and also sometimes friends and neighbors [9,10]. With increasing disability, however, care provided by relatives alone may become insufficient [6], so that about 24% of PD patients receive professional care in their home environment and 19% permanently live in a care facility [11]. Related factors to the necessity of permanent care in a nursing home are increased age, pronounced motor symptoms, cognitive dysfunction, and neuropsychiatric impairments, but especially psychotic symptoms [6,10,12]. In addition, safety concerns and caregiver-related factors such as managing changes in caregiver health play a crucial role in the institutionalization of PD patients [4]. 

Family members may experience this role change within disease progression from spouse/relative to caregiver to mere spectator due to changes in their social position, which often encompasses conflicts between patient and relatives [13]. Due to the multidimensional character of the burden, stressful situations of relatives are often not recognized in time, and relatives are therefore also considered as “invisible patients” [14]. The burden of relatives often leads to serious effects on emotional, social, physical, and financial aspects of life as well as the ever-increasing scarcity of time [14,15]. It should also be noted that the burden might not only begin with the diagnosis but with the first, initially unspecific symptoms—even for the relatives. In addition, fear of Parkinsonism/PD progression leads to a further experience of stress [16], so that overall, a significantly increased risk of a reduced quality of life and the development of depression may be the consequences [14,17,18]. However, the sample of our study does not consist exclusively of PD patients but also includes patients with Parkinsonism and their relatives to design a comprehensive support program for relatives with similar experiences.

It is already known that caregivers of patients with Parkinsonism often suffer from severe psychological stress in the late phase of the disease. The burden on caregivers increases with disability and symptoms of Parkinsonism. This is especially relevant for mental health problems such as depression, hallucinations or confusion, and falls [19]. The duration and severity of the disease correlates with the burden on the relatives [20]. They have an increased risk of psychiatric morbidity and persistent distress [21]. However, little is known about the mental attitudes and burdens of family members in the early phase of the disease [14,18]. 

The main study population does not yet correspond to the conventional definition of family caregivers, because they are not yet giving informal care. Therefore, the term “non-caregiving relatives” will be used. The sample thus includes partners of patients with Parkinsonism in the early phase of the disease (Hoehn and Yahr I–II) who live together in one household and who are not yet involved in caregiving.

Despite the growing research on the burden on caregivers of patients with Parkinsonism, there is still limited evidence on interventions for non-caregiving relatives [22]. Focusing on non-caregiving relatives is, however, of immense importance to support them as early as possible and to alleviate burdens and avoid severe strain [23]. To the best of the authors’ knowledge, there are no prevention support programs for the target population of the study. However, there is evidence of programs for diseases for which relatives are at increased risk, such as strain, (stress,) depression, and anxiety [24,25]. 

Existing support programs for family members of people with PD are often educational and provide therapeutic support but are mainly aimed at family members of patients in the late phase of the disease who are already involved in the care of the person with PD. These programs are often aimed at both PD patients and their caregivers taking part together [18,26,27,28]. This study aims to evaluate an intervention that is only aimed at the relatives.

The support program will be conducted online. Since the COVID-19 pandemic has led to digitalization in telemedicine in many areas as well as the field of neurology and the care of PD patients [29]. Nevertheless, the availability of online support programs is not yet widespread. However, approaches have been developed to examine telephone-based self-support groups [30], online teaching programs for patients with Parkinsonism in the late stage [31], and educational programs offered by healthcare professionals for caregivers [32]. Because an E-health approach is still quite uncommon, there is little data on the effectiveness of support services for caregivers. However, effectiveness has already been demonstrated in the context of preventive support for relatives in other related fields such as mental health and dementia [33,34,35].

Nevertheless, there is a lack of preventive telemedical offers for non-caregiving relatives of Parkinson’s patients [36]. The term ‘e-mental health’ refers to technological approaches that maintain or promote psychological health [37]. 

Therefore, a preventive psychological short intervention (PPSI) for non-caring relatives is to be developed within the scope of the study.

This study explicitly addresses relatives who are not (yet) involved in family care. 

The intervention itself is solely aimed at the non-caregiving relatives and intends to strengthen resources, thereby fostering empowerment in the course of a progressive disease. Topics of the intervention, which follows a cognitive–behavioral therapy approach, are, on the one hand, the visualization and activation of relatives’ social network of relationships, and, on the other hand, specific exercises with relatives of people with Parkinsonism to empower dealing with stressful situations possibly arising in the future. The intervention is offered online and allows participation from home to facilitate implementation into relatives’ everyday life. The key question is, therefore, a threefold feasibility analysis:Feasibility of the intervention: the feasibility will be assessed via acceptability, fit and subjective benefit.Feasibility of the manual (adherence): it is to be assessed whether all planned aspects of the intervention have been discussed or if there are other topics that will be brought up by the relatives.Feasibility of the study design: investigating the feasibility of the study design means critically reflecting on the mixed-methods approach, the process of a baseline measurement with post and follow-up assessments, as well as the validity of the questionnaire selection and the structure of the interview guide. The data from questionnaires will be used for exploratory analyses.

Against this background, the primary aim of this multicenter pilot trial following a mixed-methods approach is to develop and assess the feasibility of a preventive psychological short intervention to relatives of patients with Parkinsonism at early stages. In addition, the secondary aims are to investigate the effects and manual adherence of the intervention.

## 2. Methods and Study Design

### 2.1. Methods

This study will be conducted at two different locations in Germany, the Department of Neurology of the University Hospital in Marburg (study number: 175/20) and the Department of Medical Psychology/Neuropsychology and Gender Studies of the Faculty of Medicine and the University Hospital Cologne of the University of Cologne (study number: 21-1061). Ten patients and ten relatives will be included as dyads per site so that a total of 20 relatives and 20 patients with Parkinsonism will be included. Recruitment will take place separately at both sites. At the Marburg site, patients and their relatives will be recruited via an internal recruitment system of the Department of Neurology at the University Hospital that lists patients with Parkinsonism who are generally interested in participating in studies. In Cologne, recruitment will be ensured via lists of study participants from previous studies. Further, e-mail distribution lists of self-help groups will be used to increase the recruitment numbers.

Inclusion criteria for patients are: (1)Patients with a clinical diagnosis of Parkinsonism according to the Movement Disorder Society (MDS) criteria [2];(2)Patients aged ≥ 18 years;(3)Hoehn and Yahr stages I–II (OFF-state).

The exclusion criteria for the patients are:(1)Hoehn and Yahr stage ≥ III (OFF-state);(2)No care requirements and/or outpatient or inpatient care;(3)Suspected dementia according to physicians’ reports and (third-party) anamnesis.

Inclusion criteria for non-caregiving relatives are:(1)Partners of people diagnosed with Parkinsonism, living together in the same household;(2)Age ≥ 18 years;(3)Not involved in informal caregiving of the subject with Parkinsonism;(4)Willingness to use telemedicine, availability of a PC or tablet with stable internet connection;(5)No cognitive impairment (operationalized by the Montreal Cognitive Assessment [MoCA] [38], Blind Version ≥ 19; the MoCA Blind, which is suitable for online administration and therefore used here, is reduced to 22 items and converted back to 30 points maximum. A total of 19 points in the MoCA Blind version correspond to 26 points in the original MoCA “Full”);

Exclusion criteria for the relatives are: (1)Own caregiving requirement;(2)Severe depression (operationalized by the Beck’s Depression Inventory-II [BDI-II] ≥ 29 points) [39].

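### Patient exclusion criterion (2) is inverted: as worded, it rules out the early-stage patient without care needs, whose partner the study is meant to reach

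*Protocol article*

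**What the plan says.** Section 2.1 of the protocol article opens a list with the words "The exclusion criteria for the patients are" and gives as item (2) "No care requirements and/or outpatient or inpatient care". The items on either side are Hoehn and Yahr stage III or above and suspected dementia. Patient inclusion requires Hoehn and Yahr stage I–II in the OFF-state.

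For the partner, the third inclusion criterion in the same section is "Not involved in informal caregiving of the subject with Parkinsonism", and the first exclusion criterion is "Own caregiving requirement".

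The target population is described in three further places:

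- The Abstract names "family members of patients who are in an early phase of the disease, are not currently caregiving".
- The Introduction describes the sample as partners of Hoehn and Yahr I–II patients "who live together in one household and who are not yet involved in caregiving".
- Later in the Introduction: "This study explicitly addresses relatives who are not (yet) involved in family care".

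Nothing else in the article restates or corrects item (2).

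**The concern.** An exclusion list names conditions whose presence keeps a person out. Item (2) names the absence of a care need, so a patient without one is kept out. Yet that is the patient one expects to find at Hoehn and Yahr I–II with a partner who gives no care.

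This is an eligibility rule, and section 2.1 has two sites recruiting separately from different sources. If the sentence is followed, it selects the wrong patients. If staff see the slip and repair it themselves, they must decide whether any care need excludes or only care delivered by a service, and whether the care meant is nursing or medical treatment. The text settles neither question, so the patient's care status would depend on each site's repair. The Discussion and Conclusions present the study as preparation for a randomized trial, so the sentence could also be carried forward.

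**Working it through.** No arithmetic applies, and the plan gives no figure to reproduce. The check is one of logic: classify patients by whether they have a care requirement and whether they receive outpatient or inpatient care, then apply item (2) as an exclusion rule.

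- **Reading A:** the negation governs the whole phrase. A patient is excluded if there is neither a care requirement nor such care.
- **Reading B:** the negation governs only the care requirement. A patient is excluded if there is no care requirement, and also if such care is received.
- **Negation removed:** a patient is excluded if there is a care requirement or such care is received.

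| Care requirement | Receives outpatient/inpatient care | Reading A | Reading B | Negation removed |
|---|---|---|---|---|
| No | No | excluded | excluded | stays in |
| No | Yes | stays in | excluded | excluded |
| Yes | No | stays in | stays in | excluded |
| Yes | Yes | stays in | excluded | excluded |

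**First row.** This is the patient implied by early disease and a partner who is not caregiving. Both readings exclude this patient. Under reading A the and/or could also mean that lacking either feature is enough to exclude; the first row is then still excluded.

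**Who is left.** Reading A leaves only patients who need or receive care. Reading B leaves only patients who need care and receive none as an outpatient or inpatient. Their cohabiting partner must also give no informal care under the third relative criterion, so the group is close to empty.

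**Comparison within the lists.** The other patient exclusions (stage III or above, suspected dementia) and both relative exclusions (own care requirement, severe depression) name a condition whose presence excludes. Item (2) alone opens with a negation. That fits either an inclusion condition placed in the wrong list or a stray word.

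**Second row.** This row shows a further gap. If the care mentioned includes medical treatment, a patient with no care need who attends a neurology clinic falls here. Marburg recruits through the neurology department's own list, so simply deleting the negation could exclude routine neurology outpatients by accident.

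**The case against.** The strongest reply is that the intent is plain. The disease stage, the third relative criterion and the stated population all point the same way, and nobody chose to enroll patients with care needs. On this view it is a slip of wording in a small exploratory feasibility pilot, not a design flaw, and competent staff would read through it. Much of this stands: it is a wording error, and no outcome or analysis is shown to suffer if the evident intent was followed. It does not make the sentence correct, and the evident intent does not tell staff what kind of care is meant.

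Three stronger readings are tempting, and the documents do not support them.

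- A reader might infer that almost none of the 20 dyads could be enrolled, or that every dyad enrolled under the intended meaning is a protocol deviation. Both treat the journal article as the document from which the sites screen. The article gives a separate study number for each site, and the underlying documents are not shown.
- A reader might infer that the sample will be mixed on its defining attribute. That attribute is the partner's non-caregiving status, which the third relative criterion fixes clearly for both sites. What item (2) leaves open is the patient's care status.
- A reader might take it as stated that patients must have no care requirement. The Abstract and Introduction speak of the relative not giving care. A patient cared for only by professionals could have a non-caregiving partner. Even so, item (2) would still exclude patients without care needs.

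**Conclusion.** Wrong as written. Under either scope of the negation, item (2) excludes the early-stage patient without care needs and contradicts the population described in the Abstract, the Introduction and the third relative criterion.

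The conclusion rests on one inference, that the intended patient has no care requirement, drawn from the early stage and the non-caregiving partner. The size of the harm is conditional and cannot be put as a number of dyads, because it is unknown whether the site documents carry the same error and how staff applied it. The planned 10 dyads per site are a fixed number that does not depend on this item.

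**What to change.** Reconcile item (2) with the Abstract, the Introduction and the third relative inclusion criterion, in one of two ways:

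1. Keep it in the exclusion list and remove the negation, so that having a care requirement excludes the patient.
2. Move it to the inclusion list as a condition the patient must meet.

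In either case, state whether the outpatient or inpatient care mentioned means nursing care, so that routine neurology outpatients are not excluded unintentionally. Check the documents in use at Marburg and Cologne for the same sentence, and use identical wording at both. If the sites have already screened patients, record how each applied the item.

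The cost is a one-line correction at each site, with no change to sample size or study procedures.

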### 2.2. Study Design

The patients and their relatives will be informed verbally and in writing about their participation in the study. By signing the consent form, they are included in the study. Figure 1 depicts the three time points of measurement: baseline (t0), post-testing immediately after the end of the intervention (t1), and follow-up (FU) at 6 weeks post-intervention (t2). The intervention is to be understood as a preventive psychological short intervention for relatives. Patients will not participate in the intervention. No remuneration will be paid to the participants.

### 2.3. Intervention Protocol

The PPSI includes three sessions of maximum 50 min at intervals of max. 2 weeks and is to be conducted in an online meeting with the relative and a trained and supervised advisor (at least B.Sc. in Psychology or related discipline). A licensed therapist [name] trains new advisors on how to use the manual and supervises the PPSI on a weekly basis. The Red Medical platform (https://www.redmedical.de/ accessed on 3 March 2022) ensures the General Data Protection Regulation (GDPR)-compliant implementation of video consultations with overall end-to-end encryption so that conversations remain strictly confidential and cannot be accessed by third parties. The cognitive–behavioral therapy-based intervention consists of three sessions, which include the following elements: standardized elements with knowledge transfer, personalized elements addressing the individual’s perspective, and exercises to apply the knowledge on an individual basis. As support, working sheets will be used, which also serve for future implementation of the intervention elements in the study participants’ everyday life.

At a content level, the mental health of the relatives is the focus of the intervention. Each session deals with a psychological focus area. The areas are based on protective factors in prevention of mental disorders, e.g., ability to manage stress, empowerment, and social participation [40]. The most relevant areas were selected via expert panels ([name]) with regard to the most relevant issues in giving care to patients with Parkinsonism. The overarching goal is to provide self-management strategies for relatives of PD patients in the sense of “empowerment”, which can be applied at a later stage of the disease.

#### 2.3.1. Session 1—Understanding the Situation of the Relatives, Stress-Management Strategies

The first session focuses on establishing a relationship between the trained advisor and the relative as well as on exploring the personal situation and life circumstances of the relative. This includes asking about potential individual fears of disease progression. In addition, goals, wishes, and expectations towards the short intervention are discussed with the relatives. Then, a psychoeducational unit on stress management follows, containing the transfer of knowledge on the transactional stress model according to Lazarus [41]. Possible individual stressors are identified, and coping strategies are worked out in a problem-oriented or emotion-oriented way. Key questions: “what changes to the situation/action can be taken to reduce (any future) stress?” (problem-oriented coping). “How can the relative deal with the situation better?” (emotion-oriented coping).

#### 2.3.2. Session 2—Social Network and Self-Management Strategies

The second session is designed to promote self-management strategies and individual resources as well as autonomy [14,42]. First, the so-called airplane metaphor is discussed with the relatives to individually design the topic of self-care [43]. The core idea of the airplane metaphor is that every passenger in the airplane is asked as part of the safety instructions to first put on the oxygen mask themselves in case of a loss of air pressure and then to help other people [43].

Afterward, concrete methods to increase self-care will be discussed: the social (and, if necessary, professional) environment of the relatives is explored and noted in a specially provided page of the workbook. Then, with self-care in mind, it is discussed to what extent this “support network” could become active in a supportive way in the further course of the disease [9]. With the help of a visualized list, it can be possible at an early stage to identify and (re-)activate important people to the “inner circle” of the relatives.

This is followed by a unit on values orientation. Here, based on a list of values previously filled out by the relatives, they work out which personal values they feel to be important [44]. The goal is illustrated by the so-called bus driver metaphor [45]. In this imagination exercise, the relatives are asked to imagine themselves as bus drivers and to transport both positively and negatively associated passengers. The passengers symbolize negative or positive experiences and worries in dealing with Parkinsonism. Especially in the case of increasing stress (e.g., due to progression of the disease), it is helpful to activate the relatives’ personally important values and encourage them to adapt their behavior accordingly [45]. To act in accordance with personal values helps to stay psychologically flexible while experiencing interfering negative thoughts, emotions, and bodily sensations [46]. For example, a relative ruminating about Parkinsonian symptoms of their spouse will sometimes feel helpless. It could then be comforting to do something meaningful to them personally, e.g., helping others in similar situations (value: helpfulness), making the best out of the situation with the partner (relationship), or focusing on their own career (success). The relatives should be encouraged to live by their own values, regardless of their partners’ illness.

